In 2003, Cevik et al. evaluated the value of physical findings to predict fractures in patients with acute wrist trauma [8]. They included fifty-five patients in their study and concluded that edema, pain on grip and supination, pain on active and passive motion and localized tenderness can be valuable to predict a fracture.

Recently, Calco-Lorenzo et al. analyzed the possibility of creating a clinical decision rule for the assessment of conventional X-rays in acute wrist trauma [9]. They employed 46 different anamnestic and examination variables and included 179 patients in their study. They concluded that an age equal or higher than thirty-five, edema in the dorsum of the wrist, limited supination or radial deviation as compared to the contralateral wrist and pain on performing the distal radioulnar drawer test, was predictive of the presence of a distal radius fracture. However, they advised "a broader study should be undertaken to assess the feasibility of introducing a clinical decision rule".

Therefore, the primary aim of this study is to formulate a clinical decision rule to determine when an X-ray of the distal radius is necessary in patients presenting to the Emergency Department following wrist trauma.

The second aim of this study is to validate this decision rule in a new patient population and to present it as simplified risk score.

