Upon completion of the data collection in all three participating medical centers, a prediction rule will be developed based on data from two of the participating hospitals; the academic hospital and the non-academic teaching hospital. Since prediction rules always perform perfectly in the patient population they were generated from, a validation study in a new study population is required to assess its predictive quality. To ensure the most stringent form of validation, the rule will be validated in data from the third hospital, the non-teaching hospital. This method is also known as domain validation. The method of data collection in the third hospital will be similar and done simultaneously. This dataset will be comparable to the first regarding size and informative parameters and the model will be tested to verify its predictive value of the primary outcome: distal radius fracture. If necessary, the model will be updated and finally it will be presented as a simplified risk score.

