### Statistical analysis

The data from the academic hospital and the non-academic teaching hospital will be used to develop the model. The data will be assessed by using a multivariable analysis. However, to prevent too optimistic estimates of the accuracy of the diagnostic model, a more liberal p-value for statistical significance will be employed (p = 0.15). Logistic regression modeling will be used to estimate the regression coefficients and thus the log odds of a fracture versus no fracture after which a reduced model will be created by means of a log likelihood ratio test.

The accuracy of the model will be estimated by a goodness of fit test and a ROC curve. If applicable, different models can be compared using the tests mentioned above. The final model will be validated internally through bootstrapping to estimate overfitting in the calibration and discrimination stated above. By averaging the optimism an adjusted model will be generated.

Henceforth, the prediction rule will be validated in a new data set, which will be collected simultaneously in the third hospital; the non-teaching hospital. If necessary, the model will be updated using the data from the validation study, by adjusting the intercept.

Finally, the prediction model will be presented as a simplified risk score which can be used by physicians to determine the need for an X-ray in patients presenting with wrist trauma at the Emergency Department.

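### The simplified risk score is formed only after external validation, so the score physicians will use has no independent estimate of missed fractures at its cut-off

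*Protocol article*

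**What the plan says.** The Background of the protocol article sets the primary aim as a yes/no rule: to "formulate a clinical decision rule to determine when an X-ray of the distal radius is necessary". The second aim is "to validate this decision rule in a new patient population and to present it as simplified risk score", which names validation first and the score second.

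The Study procedures section keeps that order. After the test in the third hospital: "If necessary, the model will be updated and finally it will be presented as a simplified risk score".

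The Statistical analysis section gives the most detail, in this sequence:

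1. Logistic model developed in the academic and the non-academic teaching hospital, then reduced.
2. Accuracy: "The accuracy of the model will be estimated by a goodness of fit test and a ROC curve".
3. Internal validation: "The final model will be validated internally through bootstrapping to estimate overfitting in the calibration and discrimination stated above". An optimism-adjusted model follows.
4. External validation in the non-teaching hospital.
5. Conditional update: "If necessary, the model will be updated using the data from the validation study, by adjusting the intercept".
6. Last step: "Finally, the prediction model will be presented as a simplified risk score which can be used by physicians", to decide who needs an X-ray.

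The article describes no validation after step 6.

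**The concern.** What is tested and what is released differ. Steps 2 to 4 assess a regression equation. Step 6 releases a points score that must be read against a cut-off to yield an X-ray decision. Turning coefficients into points and choosing a threshold both affect who is classified as not needing an X-ray, and both come, or may come, after the third hospital's data have been used.

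For such a rule the critical error is a missed fracture, so sensitivity at the operating cut-off is the quantity a reader will want validated. Followed as written, the study can report external performance for the model but gives no independent sensitivity, negative predictive value or proportion of X-rays avoided for the score at its cut-off. If the intercept is refitted on the third hospital, or the cut-off is picked with its results in view, that hospital has become development data for the released product.

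**Working it through.** **The plan's own figure.** The Sample size section gives 20 candidate parameters and ten events per parameter: 20 × 10 = 200 fractures, which reproduces the stated minimum. At about 50% fractures this needs 200 / 0.50 = 400 patients. The planned 500 give 500 × 0.50 = 250 fractures.

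**Object at each step.**

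| Step | Object | Data |
|---|---|---|
| Fit, ROC, bootstrap, shrinkage | model | two development hospitals |
| External validation | model or rule | third hospital |
| Intercept update (conditional) | model | third hospital |
| Simplified score | score | no data named, no later test |

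**What an intercept update does.** Under a fixed absolute-risk cut-off c, a patient is X-rayed if a + xb ≥ logit(c). After an update by d, the condition is a + xb ≥ logit(c) − d on the original scale. Take c = 10% and d = ±0.4, both assumed for illustration: logit(0.10) = −2.197. With d = +0.4 the equivalent original cut-off is −2.597, a risk of 6.9%. With d = −0.4 it is −1.797, a risk of 14.2%. Ranking, and so the AUC, does not change. Under a cut-off expressed in points, or set by a target sensitivity, the intercept drops out and nobody is reclassified. The article does not state which kind of cut-off will be used.

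**Illustrative simulation.** All inputs are assumed: 8 binary predictors, 500 patients per set, a validation intercept lower by 0.7, a cut-off at 15% predicted risk, 500 runs.

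- Intercept update: AUC 0.782 before and after; mean sensitivity at the fixed risk cut-off fell from 98.2% to 93.7%.
- Rounding to points, with the points cut-off set in the development data: AUC 0.779; sensitivity differed from the un-updated model by a median of 0.5 percentage points (97.5th percentile 2.1).

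Rounding alone is a small matter. The cut-off and the update matter more, and the AUC does not respond to either.

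**Could the planned data validate a frozen score?** The article aims for a validation set as large as the development set. Assuming 500 patients at 50%, that is 250 fractures. Exact (Clopper-Pearson) 95% intervals for sensitivity:

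| Detected / fractures | Sensitivity | 95% CI |
|---|---|---|
| 225/250 | 90% | 85.6–93.4% |
| 238/250 | 95.2% | 91.8–97.5% |
| 245/250 | 98% | 95.4–99.3% |
| 250/250 | 100% | lower limit 98.5% |
| 196/200 | 98% | 95.0–99.5% |
| 98/100 | 98% | 93.0–99.8% |

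The last two rows allow for fewer fractures, because the article gives no separate volume for the third hospital.

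**The case against.** The strongest reply is that the score is only a way of presenting a rule that has already been validated. The Background promises "The second aim of this study is to validate this decision rule in a new patient population", and the article speaks elsewhere of validating the rule. A threshold could be carried into validation, and a condensed article may leave its value to a fuller document. This stands in part: the absence of a stated cut-off or target sensitivity is not itself the fault. But three sections place the score last, and none says that the score and its cut-off exist before the third hospital is analysed.

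A reader might infer more than the text supports:

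- *That the named measures say nothing about sensitivity.* A ROC curve shows the model's sensitivity and specificity at every cut-off. With the fracture proportion, X-rays avoided follow as (1 − sensitivity) × prevalence + specificity × (1 − prevalence). The gap concerns the final score at its chosen cut-off.
- *That updating on the third hospital is certain.* It is conditional. Without it, that hospital played no part in fitting the model.
- *That an update will move patients across the line.* It does so only under a fixed absolute-risk cut-off, which the article does not state.
- *That overfitting of the slope goes unaddressed because only the intercept is updated.* Shrinkage is planned before external validation (Abstract and Statistical analysis). It does not guarantee a slope of 1 in a different type of hospital, but it is the relevant safeguard.
- *That models will be ranked by fit-test p-values.* The reference back to the tests already named can include the likelihood ratio test and the ROC curve.

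**Conclusion.** The point holds in a limited form. The article validates the model, updates it on the validation hospital if needed, and then forms the score, with no later test. As written, the second aim is not met for the released score at its operating cut-off. The third hospital loses its independence if an update is made or the cut-off is chosen after its data are seen.

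It would be too strong to say that nothing about the rule's sensitivity is validated: the model's ROC curve in the third hospital would be informative, and the simulated effect of rounding is small. The size of any loss cannot be derived from the article; the intercept and simulation figures rest on assumed inputs, and the 250 validation fractures rest on 500 patients at 50%. This should be fixed, but it does not invalidate the design, since the data needed are already planned.

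**What to change.** In Study procedures and Statistical analysis, reorder the steps:

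1. Derive the simplified score and its cut-off from the shrunken model in the two development hospitals, with the criterion for choosing the cut-off stated.
2. Freeze both in a dated record before the third hospital's outcomes are analysed. This matters because the rule is to be developed only after data collection has ended at all three sites.
3. Apply the frozen score in the third hospital. Report sensitivity, negative predictive value and the proportion of X-rays avoided with exact 95% CIs, alongside the c-index and calibration.
4. Report any version updated on the third hospital separately, labelled as not externally validated.

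The cost is a changed order of analysis, a freeze note and possibly a slight loss of AUC from rounding. No additional patients or data items are needed.

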## Methods/Design

This study consists of two components in which the data will be collected cross-sectionally. The data will be collected in three different hospitals during a period of six months. The participating hospitals include one university hospital, one non-academic teaching hospital, and one non-teaching hospital.

One component of this research comprises a study which will be performed to determine which combination of clinical parameters has a predictive value for the presence of a distal radius fracture in adult patients presenting to the Emergency Department following acute wrist trauma. This will be done by creating a model from the data collected in the university hospital and the non-academic teaching hospital. This model will be internally validated by bootstrapping. In the second component of this study, the developed prediction model will be validated in a new dataset. This dataset will be collected simultaneously in the third hospital, the non- teaching hospital, using the same approach as in the other hospitals.

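### In the stated sequence the third-hospital validation covers the regression model, and no validation of the simplified risk score or its cut-off is planned

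*Protocol article*

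**What the plan says.** The Background sets a primary aim, to "formulate a clinical decision rule to determine when an X-ray of the distal radius is necessary", and a second aim, "to validate this decision rule in a new patient population and to present it as simplified risk score".

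Under Statistical analysis the steps run as follows. A logistic model is fitted on data from the university and the non-academic teaching hospital and reduced by likelihood ratio tests, with a significance level of 0.15. It is assessed by goodness of fit and a ROC curve and bootstrapped, and then "By averaging the optimism an adjusted model will be generated". After that, "Henceforth, the prediction rule will be validated in a new data set, which will be collected simultaneously in the third hospital". An update is allowed if needed; it uses the third hospital's data and is confined to the intercept. The last step reads: "Finally, the prediction model will be presented as a simplified risk score which can be used by physicians".

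Study procedures gives the same order: "If necessary, the model will be updated and finally it will be presented as a simplified risk score". Methods/Design names the validated object: "In the second component of this study, the developed prediction model will be validated in a new dataset".

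No section says that the points, or a cut-off on them, will be tested in any data.

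**The concern.** A simplified score is generally not the same instrument as the regression it comes from. Coefficients are rounded or replaced by unit weights, the number of distinct values falls, and so does the choice of cut-offs. The article intends the score to decide who gets an X-ray, so its performance at the chosen cut is what matters in practice. Study procedures itself argues that a rule must be tested in a new population before its predictive quality can be known. By that standard, the issued tool has no planned external assessment.

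The risk is that the model's third-hospital results are read as the score's. There is a second, smaller risk. Model development starts only once data collection is complete in all three hospitals. If the points and cut-off are chosen last, they may be chosen with the third hospital's results in view, and that hospital is then no longer an independent test of them.

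**Working it through.** **1. Order of steps**

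| Step | Statistical analysis | Study procedures |
|---|---|---|
| Develop | logistic model, reduced, optimism-adjusted | rule from two hospitals |
| Validate in third hospital | prediction rule | rule, then called the model |
| Update | conditional, intercept only | conditional |
| Simplify to a score | last | last |
| Test the score | not described | not described |

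The two sections agree, and neither places the score before validation.

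**2. Data available** (Sample size section)

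- Stated minimum: 20 parameters / 0.10 = 200 fractures, which reproduces the article's figure.
- At about 50% fractures: 200 / 0.50 = 400 patients. The planned 500 give 500 × 0.50 = 250 fractures, or 250 / 20 = 12.5 per parameter.
- The validation set is meant to equal the development set, so about 500 patients and 250 fractures.

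**3. What the intercept update can change**

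Adding a constant to every linear predictor leaves the ranking of patients, the ROC area and the points unchanged. It changes predicted risks and any cut defined on the risk scale.

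**4. Can simplification change performance?**

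The article gives no coefficients, so the effects are assumed. Simulation: 20 independent yes/no signs, each present in 40% of patients, 8 of them informative; about 50% fractures; 500 development and 500 validation patients; signs kept at p < 0.15; 300 runs at each of three effect sizes. Rounded points are each coefficient divided by the smallest absolute coefficient, rounded to an integer. No shrinkage was applied. The cut was set for at least 97% sensitivity in the development data; that target is an assumption, since the article states none.

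Mean results in validation data (weak / middle / strong effects):

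| | Model | Rounded points | One point per sign |
|---|---|---|---|
| ROC area | 0.610 / 0.708 / 0.781 | 0.608 / 0.706 / 0.778 | 0.600 / 0.684 / 0.743 |
| Sensitivity at the cut | 0.967 / 0.961 / 0.962 | 0.979 / 0.973 / 0.972 | 0.983 / 0.981 / 0.981 |
| Specificity at the cut | 0.068 / 0.150 / 0.232 | 0.046 / 0.112 / 0.188 | 0.036 / 0.080 / 0.124 |

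Differences from the model:

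- ROC area: 0.002 / 0.002 / 0.003 lower for rounded points; 0.010 / 0.024 / 0.038 lower for one point per sign.
- Specificity: 2.2 / 3.8 / 4.4 percentage points lower for rounded points; 3.2 / 7.0 / 10.8 lower for one point per sign.
- Sensitivity: 1.0 to 1.2 points higher for rounded points; 1.6 to 2.0 higher for one point per sign.

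**5. How much of the specificity gap is real loss?**

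The scores above sit at a higher sensitivity than the model, so part of the gap is only a different operating point. Two further simulations with assumed effects compared them at an equal 95% sensitivity. One used 500 patients, 50% fractures, 20 correlated yes/no signs, likelihood ratio selection at 0.15 and 80 runs per scenario, with model ROC areas of 0.757 and 0.838. Across the two, rounded points lost 0.1 to 0.8 points of specificity and one point per sign lost 1.5 to 5 points. ROC area losses for rounded points were 0.001 to 0.004; for one point per sign, where reported, they were 0.009 to 0.017.

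**6. Precision if the score is validated in the third hospital**

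Half-width of the 95% CI for sensitivity = 1.96 × √(s(1 − s)/250). For an assumed s of 0.95, 0.97 or 0.99 this is 2.7, 2.1 or 1.2 percentage points. The planned data set can support the analysis.

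**The case against.** The strongest reply is that presenting a model as a score may be a matter of format. The article uses rule, model and score loosely, a condensed article may leave score construction to a fuller document, and finely rounded points perform almost like the model. Much of this stands. How points are built is no omission here, and the discrimination at stake may be tiny. What it does not answer is the sequence, which the article states twice and which a fuller plan following it would inherit.

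Four stronger readings are tempting, and the documents do not support them.

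- *The second aim is not met.* The aim asks for the decision rule to be validated and for it to be presented as a score. The plan does both. The aim fails only if the decision rule is taken to mean the points score itself.
- *No data are left to test the score.* The third hospital's patients can be scored. The only permitted update is to the intercept, which does not enter the points, so the update carries nothing from that hospital into them. What is missing is a plan to do the test with points and cut-off fixed beforehand.
- *The overfitting correction is lost because uniform shrinkage cancels out of the points.* This presumes one way of making points (ratios of coefficients) and a single shrinkage factor. The article states neither, and relative weights that do not change under uniform shrinkage are not a defect.
- *The specificity gap at a development cut can be turned into a count of X-rays wrongly called avoidable.* Most of that gap comes from the coarser score landing at a higher sensitivity, as step 5 shows, and the article names no target sensitivity.

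**Conclusion.** The point holds as a gap between what is validated and what is issued. Both descriptions of the analysis put the score after the external validation and any update, and no validation of the score or its cut-off is planned. The consequence depends on how coarse the score is: negligible in ROC area for finely rounded points, about 0.01 to 0.04 for one point per sign, with shifts in sensitivity and specificity at any cut chosen in development. These sizes rest on assumed effects, selection and cut-offs, and show only that the model's results need not carry over to the score. The sequence itself is read directly from the article. This should be corrected; it does not undermine the study's design or data.

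**What to change.** Reorder the steps in Study procedures and Statistical analysis:

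1. Using only the two development hospitals, derive the integer points, the cut-off and a score-to-risk table based on the optimism-adjusted model. Freeze all three before the third hospital's outcomes are analysed. The choice of cut-off stays with the investigators.
2. In the third hospital, report the frozen score's ROC area, calibration (observed against predicted risk by score value), and sensitivity and specificity with confidence intervals. Show the unrounded model alongside.
3. If the intercept is updated, change only the score-to-risk table and state that the updated table has not been externally validated.

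If the present order is kept, the report should say plainly that the score still needs validation.

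Cost: changed wording and order of analysis, with no further patients or data. The reported accuracy may be slightly less favourable than that of the unrounded model.

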## Ethical considerations

### Regulation statement

The study will be conducted according to the principles of the Declaration of Helsinki (59th World Medical Association General Assembly, Seoul, October 2008) and in accordance with the Medical Research Involving Human Subjects Act (WMO).

### Recruitment and consent

Patients with acute traumatic wrist injury will be treated by the physician on call in the Emergency Department. The only difference is that clinical parameters, as recorded during the physical examination will be more extensive and will be recorded more precise by the treating physician. Because of the observational character of this study, no informed consent was deemed necessary by the Medical Ethical Review Committee of the Academic Medical Center of the University of Amsterdam. This committee stated on March 17, 2011 that The Medical Research Involving Human Act (WMO) does not apply to this study and that an official approval by the committee is not required, reference number; project 2011_078.

## Administrative aspects and publication

### Handling and storage of data and documents

The data will be coded by patient number. Research data will be stored in a database (PASW statistics 18 and Microsoft Excel), and will be handled confidentially and anonymously. Research data that can be traced to individual persons can only be viewed by authorized personnel. These persons are the members of the research team, members of the health care inspection, and members of the Medical Ethics Committee of the Academic Medical Center Amsterdam. Review of the data may be necessary to ensure the reliability and quality of the research. The handling of personal data is in compliance with the Dutch Data Protection Act (in Dutch: 'Wet Bescherming Persoonsgegevens', WBP) and the privacy regulation of the Academic Medical Center Amsterdam.

